### Objectives

The aim of the PYloroplasty versus No Intervention in GAstric REmnant REconstruction after Oesophagectomy (PYNI-GAREREO) trial is to compare the postoperative change in body weight between patients undergoing mH-P and no intervention (NI). The change in body weight after mH-P mainly reflects the nutritional status caused by the change in oral intake. The primary outcome is the rate of body weight loss at 6 months postoperatively.

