#### Decompression tube placement and jejunostomy

We will routinely perform decompression tube placement and jejunostomy of the gastric remnant. After mobilization of the stomach, we will cut the gastric serosa and muscular layer. We will then cut the point of the mucosa layer and insert two tubes: the decompression tube (inserted cranially) and the enteral tube (inserted caudally toward the jejunum). The two tubes will be placed in the gastric remnant wall by the Witzel procedure. Finally, after the reconstruction and cervical anastomosis, we will perform abdominal wall plasty of the gastric remnant with the placement of tubes.

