### Outcomes

The primary endpoint is the rate of body weight loss at 6 months after surgery. The secondary endpoints are oral intake and change in nutritional status, which will be checked during the perioperative hospitalization period and at 1, 3, 6, 9, and 12 months after surgery.

Oral intake will be calculated as a percentage of total energy expenditure, which will be calculated based on the weight and activity coefficient of each patient, and data will be collected at each time point. As the nutritional status of the patient will be monitored by body composition which is analyzed by a bioimpedance analyzer (InBody S10®). The analyzer determines the total body fat mass (kg) and skeletal muscle index (kg/m^2^). Additionally, blood tests will be performed at fixed points to measure nutritional evaluation indices (albumin, pre-albumin, cholesterol, total protein, lymphocyte count, and C-reactive protein).

Intraoperative factors such as the total blood loss, operation time, thoracic approach, subtotal gastric remnant or gastric tube reconstruction, and inclusion or exclusion of Kocher mobilization will also be analyzed.

To evaluate the degree of pyloric transit as a secondary endpoint, the amount and nature of decompressed gastric drainage and the pH and bilirubin level of the drainage will be measured on postoperative days 1, 3, 5, and 7. On day 7, the degree of pyloric drainage and the presence or absence of reflux will be assessed by oral contrast according to the standard clinical path. The blood and gastric drainage measurements will be taken in the laboratory, the data will be recorded in the medical record, and the sample will be discarded. The decompression tube will be clamped at 6:00 am to equalize the condition of the reconstructed elevated stomach, and contrast examination will be performed at 9:00 am on the same day. The contrast medium will be barium diluted to 60%.

The pyloric transit (an objective index) as evaluated by oral barium contrast will be scored according to the presence or absence of gastric contents in the reconstructed elevated stomach at the beginning of the examination (0: no, 1: yes), the pyloric transit time of the contrast medium (0: < 1 s, 1: > 1 s), and stagnation of the contrast medium in the stomach (0: completely disappears; 1: more than half remains; 2: all remains).

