Do you break out in a cold sweat within about 30 min after eating?	□	□	□	□	□
Do you experience palpitations within approximately 30 min after eating?	□	□	□	□	□
Do you experience dizziness within approximately 30 min after eating?	□	□	□	□	□
Does your stomach rumble within about 30 min after eating?	□	□	□	□	□
Do you have abdominal pain within about 30 min after eating?	□	□	□	□	□
Does your whole body become sluggish and weak 2 to 3 h after eating?	□	□	□	□	□
Do you feel sleepy 2 to 3 h after eating?	□	□	□	□	□
Do you break out in a cold sweat 2 to 3 h after eating?	□	□	□	□	□
Do you have diarrhea?	□	□	□	□	□

The short-term outcomes evaluated in this study will be postoperative complications and the length of hospital stay. Postoperative complications in this trial are defined as anastomotic leakage, stricture, pneumonia, recurrent nerve palsy, surgical site infection, and chylothorax.

The routinely placed jejunostomy enteral tube will be removed within 3 months postoperatively in the outpatient clinic when the patient has been determined to have no risk of reduced oral intake. If the tube feeding is used for a longer period, the prolonged time will be one of the outcome parameters.

Long-term recurrence and the prognosis will also be followed up.

Patients will be blinded to which group they are in, but the physician who performs the surgery and performs the imaging and follow-up will not be blinded to whether pyloroplasty is performed. The dietitian, nurse, and data analyst who evaluate the nutritional status and gastrointestinal symptoms will be blinded to which group each patient is in.

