### Statistical methods

The Mann–Whitney *U*-test will be used to compare continuous variables such as weight change, which is the primary endpoint; body composition; and blood test indices. Student’s *t*-test (two-tailed) will be used to compare the mean parameters, and the chi-square test will be used to compare the bivariate variables such as the presence of perioperative complications.

Further subgroup analysis will only be carried out in case of significant interaction effects. The Wilcoxon signed rank test will be used to determine significant effects. Comparisons between the mH-P and control group for weight change either pre- or postoperative 6 months will be performed. Differences with a *p* < 0.050 are considered statistically significant.

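### Tube feeding counts as an outcome only once it runs past 3 months, so earlier differences between the arms go uncounted and 6-month weight is harder to read as a result of oral intake

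*Protocol article*

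**What the plan says.** The protocol article places a feeding tube in everyone: "We will routinely perform decompression tube placement and jejunostomy of the gastric remnant" (Decompression tube placement and jejunostomy). Under Outcomes, the tube is to be "removed within 3 months postoperatively in the outpatient clinic when the patient has been determined to have no risk of reduced oral intake". For feeding that goes on longer, the same section adds: "If the tube feeding is used for a longer period, the prolonged time will be one of the outcome parameters".

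The primary endpoint makes no reference to tube feeding: "The primary endpoint is the rate of body weight loss at 6 months after surgery" (Outcomes). Under Statistical methods, the Mann–Whitney test "will be used to compare continuous variables such as weight change, which is the primary endpoint". The Objectives section tells the reader how to interpret weight: "The change in body weight after mH-P mainly reflects the nutritional status caused by the change in oral intake".

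Oral intake is measured in its own right, as a secondary endpoint assessed in hospital and at 1, 3, 6, 9 and 12 months: "Oral intake will be calculated as a percentage of total energy expenditure" (Outcomes). On blinding, the same section states that "the physician who performs the surgery and performs the imaging and follow-up will not be blinded to whether pyloroplasty is performed", while the dietitian and nurse who assess nutritional status are blinded.

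**The concern.** There are two linked problems.

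The first is the tube-feeding outcome. Dependence on the tube is a direct consequence of poor oral intake, which pyloroplasty is meant to prevent. All patients start with a tube, so the time until it is no longer used is defined for every randomised patient. The stated outcome discards most of that information. It starts counting at 3 months and supplies a duration only for patients who get that far. Whether a patient gets that far may itself depend on the allocated procedure, so a comparison of prolonged times among those patients is not a randomised comparison.

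The second is the reading of the primary endpoint. Feeding past 3 months is reserved in effect for patients whose oral intake is in doubt. In such a patient, weight at 6 months can reflect tube calories as well as food eaten. If the control arm has more of these patients, as the trial's hypothesis implies, weight could look similar in the two arms although intake differs. A null result on weight would then be hard to interpret without good data on tube feeding by arm.

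**Working it through.** **Step 1: what the stated outcome can detect.** Write T for the time from surgery to the end of tube feeding. The stated outcome is in effect T minus 3 months when T exceeds 3 months, and otherwise zero or undefined. Take one patient whose feeding ends at 3 weeks and another at 12 weeks (illustrative times, both inside 3 months). Total duration differs by 12 − 3 = 9 weeks. The stated outcome treats the two as identical. The same holds between the arms: any difference that arises and resolves within 3 months is invisible. If patients without prolonged feeding are set to zero, the outcome covers everyone but remains blind to this period. If they are left out, it is also confined to a subgroup selected after randomisation.

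**Step 2: the planning figures.** Sample size gives mean weight loss of 4.2% with pyloroplasty and 8.2% without, so the planned difference is 8.2 − 4.2 = 4.0 points. It also gives two-sided α = 0.05, power 0.80 and 60 per arm before loss to follow-up. No SD is stated, so the 60 cannot be reproduced. It can only be solved for the SD it implies:

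SD = 4.0 × √(60/2) / (1.960 + 0.842) ≈ 7.82 points.

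**Step 3: a sensitivity range for the weight comparison.** Let f be the share of an arm still tube-fed close enough to month 6 to affect weight, and g the weight preserved by feeding, in percentage points. Neither is in the document; both are assumptions. Then

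- difference seen = 4.0 − g × (f in control − f in pyloroplasty)
- power ≈ Φ(difference × √(60/2) / 7.82 − 1.96)

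This is a two-means approximation with 60 evaluable patients per arm. Any change in the SD is ignored.

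| f control / f pyloroplasty | g | Difference seen | Power |
|---|---|---|---|
| 30% / 30% | 2 to 6 | 4.0 | 80% |
| 10% / 5% | 2 to 6 | 3.9 to 3.7 | 78% to 74% |
| 20% / 10% | 2 to 6 | 3.8 to 3.4 | 76% to 66% |
| 30% / 10% | 2 to 6 | 3.6 to 2.8 | 71% to 50% |
| 10% / 20% | 2 to 6 | 4.2 to 4.6 | 84% to 90% |

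For example, with 30% against 10% and g = 6, the difference is 4.0 − 6 × 0.20 = 2.8.

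**Step 4: what the range means.** Equal use gives no attenuation, and heavier use in the pyloroplasty arm reverses its sign. The table also assumes that 4.0 points is the difference free of tube-feeding effects. That figure comes from 20 retrospective patients, and the article does not say how they were tube-fed. If they were managed in the same way, 4.0 is already a net figure and nothing further should be subtracted.

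**The case against.** The strongest reply is that comparing weight whatever feeding support a patient receives is a legitimate treatment-policy question, and that the Objectives section says only that weight mainly reflects intake, which leaves room for other contributors. This stands: the primary comparison is not wrong and need not be replaced.

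It is also fair that tube duration is not the only safeguard. Oral intake is a secondary endpoint at every visit, and pyloric transit and eating symptoms are assessed as well. A tube-fed patient who cannot eat would be told apart from one who eats normally on the oral-intake endpoint at the same visit. A reader might infer that poor intake in the first 3 months goes unrecorded. It does not; what goes uncounted is tube dependence in that period.

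A reader might also infer that unblinded clinicians drive how long feeding lasts. The article says that the follow-up physician is unblinded and that removal takes place in the outpatient clinic, but not who decides on it. This is a possibility, not a finding.

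Finally, handling rules for tube-fed patients may stand in the full protocol or analysis plan, and tube calories may already be on the case record form. Their absence from an article is not held against the trial. None of this answers the point about the prolonged-time outcome, which is a stated definition and not an omission.

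**Conclusion.** The point holds in a limited form. The tube-feeding outcome is badly fixed: it ignores the first 3 months and yields a duration only for a subgroup formed after randomisation. This follows from the text alone and needs no assumption.

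The effect on the primary endpoint is conditional. If tube use differs by arm and lasts long enough to affect weight at month 6, part of the weight comparison reflects tube calories, and the Objectives section's reading of weight becomes less secure. Under the trial's own hypothesis the pull would be towards no difference, but the document does not establish this.

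A tempting stronger claim is that the weight difference is diluted by a known amount, for instance 10 to 30% of the planned effect: 0.10 × 4 = 0.4 to 0.20 × 6 = 1.2 points out of 4.0, taking 15 to 25% tube-fed in the control arm, 5% in the pyloroplasty arm and 4 to 6 points preserved. Every input but the 4.0 is assumed, the range excludes zero only because unequal use was put in, and the 4.0 may already contain the effect. No size should be attached to the attenuation. The change is worth making because it is nearly free, and a null weight result would be hard to interpret without it.

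**What to change.** Leave tube removal as it is and change the outcome and its reading.

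1. Replace the prolonged time with the total duration of tube feeding from surgery in all randomised patients, compared by arm as time to end of tube feeding. State how death while still tube-fed is handled.
2. Keep 6-month weight as the primary comparison, and state that it is made regardless of tube feeding.
3. Record at the 6-month visit whether the patient is still tube-fed.
4. Interpret a weight difference, or its absence, as driven by oral intake only when read jointly with the oral-intake endpoint and tube-feeding duration by arm.

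An analysis that ranks patients still tube-fed at 6 months below all others is at most an optional sensitivity analysis. Tube status may reflect unblinded decisions, or complications such as leakage, stricture or recurrent nerve palsy that are distinct from delayed emptying, so such a ranking would not isolate the effect of interest.

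The cost is a little more data (the date feeding ended and tube status at an existing visit), a wording change, and one more secondary comparison to report. The primary analysis does not change. Since the trial is already recruiting, the redefinition should be dated and made before tube-feeding data are examined by arm.

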### Sample size

The primary endpoint of this trial is the determination of the rate of change in the postoperative body weight. The sample size required to predict the number of patients necessary for statistical validity (two-sided test) is based on our retrospective data from June 2019 to June 2020 (*n* = 20). These are unpublished data. According to these data, the average rate of body weight loss at 6 months postoperatively is − 4.2% in the mH-P group and − 8.2% in the NI group. The incidence rate of the average body weight loss in the mH-P group is expected to be ≤ 4%. We calculated that 60 patients will be required in each arm of this study with a significance (*α* level) of 0.05 and power (1 − *β*) of 0.8. Anticipating a 5% rate of loss to follow-up, we calculated that 70 patients will be required in each arm of this study (total study population of 140 patients).

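### Sample size: 60 patients per arm with 5% loss to follow-up gives 64 per arm, not the stated 70

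*Protocol article*

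**What the plan says.** All the inputs stand in the Sample size section of the protocol article. The calculation is for a two-sided test and draws on 20 unpublished retrospective patients. Mean weight change at 6 months was −4.2% with pyloroplasty and −8.2% without. The section then says: "We calculated that 60 patients will be required in each arm of this study with a significance" level of 0.05 and "power (1 − *β*) of 0.8". The next step is "Anticipating a 5% rate of loss to follow-up, we calculated that 70 patients will be required in each arm of this study", making 140 in total. The Abstract (Methods) and Table 3 repeat the target of 140, and Table 3 splits it 70 and 70.

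Between the retrospective means and the figure of 60 stands one more sentence: "The incidence rate of the average body weight loss in the mH-P group is expected to be" ≤ 4%.

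**The concern.** The section presents 70 as the calculated result of allowing 5% loss on 60. A 5% allowance adds only three or four patients to 60, not ten. At least one of the three printed figures, or the reason given for the last step, is therefore wrong as written.

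Two things depend on it. First, the sample size is the justification for the number of patients randomised to have or not have a surgical procedure, and 12 of the 140 have no stated justification. Second, a reader who later asks how many missing 6-month weights the design can bear finds two answers: 5% of 140 is 7 patients, while 140 − 120 is 20.

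**Working it through.** **Inputs (all from Sample size):** 60 evaluable per arm, 5% loss, 70 per arm after loss, 140 in total.

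**1. The plan's own step, standard formula n/(1 − d).**
- Per arm: 60/(1 − 0.05) = 63.2, rounded up to 64; total 128.
- On the total: 120/0.95 = 126.3, rounded up to 127.
- Stated: 70 and 140. Not reproduced; short by 6 per arm.

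**2. The add-on variant n × (1 + d).** 60 × 1.05 = 63. Not 70.

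**3. The loss rate that 70 implies.** 1 − 60/70 = 0.143, or 14.3%. As an add-on, 10/60 = 16.7%. For comparison:
- 10% loss: 60/0.90 = 66.7, so 67.
- 15% loss: 60/0.85 = 70.6, so 71 (69 as an add-on).

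Only a loss rate of about 14 to 15% comes near 70.

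**4. Could the primary test account for it?** The Statistical methods section says the Mann–Whitney test "will be used to compare continuous variables such as weight change, which is the primary endpoint". If 60 was sized for a comparison of means and is inflated by the normal-theory efficiency of 0.955, then 60/0.955 = 62.8, and 62.8/0.95 = 66.1, so 67. The worst-case efficiency of 0.864 gives 60/0.864 = 69.4, so 70 before any loss, but 69.4/0.95 = 73.1, so 74 after it. Neither gives 70 with a 5% loss.

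**5. Could an unstated further allowance account for it?** Arithmetically, yes. Since 70 × 0.95 = 66.5 and 66.5/60 = 1.108, an extra inflation of roughly 10% would do; for example 60 × 1.10/0.95 = 69.5, so 70. The article states no such allowance.

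**6. Direction.** With 70 per arm and 5% lost, 66.5 per arm remain, against 60 required. If 60 gives exactly 80% power, the normal approximation at 66.5 gives (1.960 + 0.842) × √(66.5/60) − 1.960 = 0.99, a power of about 84%. This figure takes the 60 as given and does not verify it.

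**7. The assumed difference.** The retrospective means differ by 8.2 − 4.2 = 4.0 points. If the pyloroplasty mean was instead set at 4% or less, the difference is 8.2 − 4.0 = 4.2 points or more. The text does not say which entered the calculation.

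**The case against.** The strongest reply is that nothing is harmed. The error is on the safe side, 140 is used consistently throughout, and no analysis or conclusion changes. The investigators may simply have rounded up, or added patients for the two planned interim analyses, since the Trial status section mentions an adjusted α level. Most of this stands, and it limits the weight of the point. It does not reconcile the figures: the section says 70 was calculated, names only the 5% loss as the reason, and uses α = 0.05. If rounding or interim looks were the reason, the stated reason is wrong.

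A reader might infer more than the article supports:

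- **That the 60 is unsound because no SD is given.** A journal article may leave the SD to the full protocol. For a 4.0-point difference, 60 per arm fits an SD of about 7.8 points, but that value is obtained by assuming 60 is right. The 60 cannot be checked here; it is not shown to be wrong.
- **That the trial should have been sized for Mann–Whitney.** The adjustment is about 3 patients per arm, and the 0.955 holds only under normality. Sizing on means and testing on ranks is common practice.
- **That attrition would be monitored against the wrong threshold.** Neither Recruitment nor Oversight and monitoring sets an attrition trigger.
- **That 4.2% and ≤ 4% contradict each other.** The first is what was observed and the second what is expected, so they can differ. Calling an average an incidence rate is loose wording.

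**Conclusion.** The point holds for the step from 60 to 70. With 60 evaluable patients per arm and 5% loss, the requirement is 64 per arm (128 in total), not 70 (140). The printed total corresponds to 14.3% loss. The discrepancy is 6 per arm, 12 overall, too large for rounding to a whole patient, and the article gives no other explanation.

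It is an internal contradiction in the conservative direction, so it is a correction that should be made rather than a threat to the trial. The statement that no power is lost rests on 60 being the right evaluable number, which the article alone cannot confirm. The documents also do not show which element is wrong: the loss rate, the total, or the reason given.

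**What to change.** Keep 140 and rewrite the paragraph so that its figures agree. The sponsor should confirm which of these was intended:

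- **Restate the allowance:** 60 evaluable per arm are needed, and 70 per arm covers about 14% of patients without an evaluable 6-month weight. If 5% remains the honest expectation, say so separately from what the design tolerates.
- **State the further reason:** 60 evaluable per arm become 64 after 5% loss, and the number was raised to 70 for a named reason, with its size.

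In the same edit, replace the sentence about an incidence rate of ≤ 4% with the mean difference that entered the calculation (4.0 points if the retrospective means were used).

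The cost is one corrected paragraph. Enrolment, randomisation and analysis are unchanged.

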### Recruitment

Surgeons and CRCs will check the inclusion and exclusion criteria 1 to 2 days before an eligible patient visits their outpatient clinic. Inclusion rate feedback will be provided every 6 months in a monitoring report. Completeness of case record form (CRF) data and adherence to the study protocol will be checked on a weekly basis by the coordinating investigator or CRC. This trial is advertised to make potential participants aware of and thus recruited by the study outline published on the Teine Keijinkai Hospital homepage.

### Data collection and management

A participant number will be generated upon each patient’s inclusion in the study, and this number will be used for further identification in the database. The participant number key is accessible by the coordinating investigator. Clinical data will be collected by the study coordinator or clinical research nurse and will be recorded in a good clinical practice-compliant digital CRF and database. All non-electronic items containing data will be kept in locked cabinets at the data coordinating centers.

The data will be able to be accessed by the research nurse and research physician. After the study has been completed, requests to access the dataset can be submitted to the project leader or principal and coordinating investigator. The completed CRFs will also be checked with the source data regarding the primary outcome parameter and important secondary outcome parameters.

Data will be collected via datasheets on paper and kept securely. All handling cases will be managed by subject identification code or anonymized registration number. The correspondence table of the anonymizing code and names and the consent form containing the names will be kept strictly in the separate lockable document storage at Teine Keijinkai Hospital Clinical Research Center.

